### Intervention

The main interventions of the study include:

(a) a programme of individualised psycho-educational instruction focusing on behaviours prior to and during a illness related crisis,

(b) the distribution of an individualised crisis card containing essential information and guidelines for preventing an acute crisis or for acting properly prior to or during a relapse, and

(c) a 24-month preventive monitoring of individual risk factors of relapse or inadequate disorder-treatment-related behaviour.

All measures are provided by a personal mental health care worker (psychologist), who will be available and maintain permanent contact to the patient throughout the intervention and follow-up period of the study.

The intervention programme shall not replace the patients’ regular therapy. Rather, it is considered as a supplementary measure to give chronically mentally ill patients individual support to become more actively involved in their care. Because the programme targets an increase in the patient’s empowerment, no structured collaboration between the personal mental health care worker and the regular treatment team is intended. The regular (inpatient) treatment team is informed that a patient is participating in the study. Members of the regular treatment team, however, are not aware of the outcome of randomisation.

(a) Individualised psycho-educational instruction of study patients

Immediately after recruitment and randomisation, each study patient in the intervention group attends the initial (1–3) instruction sessions. These sessions address information on relapses in mental disorders, treatment and adequate behaviour to prevent a crisis. The sessions are scheduled prior to discharge from the index episode (inpatient stay in the study centres) and individually adapted to the specific needs, experiences and history of illness of the respective patient. The series of initial sessions aims to establish a good relationship between the patient and the personal mental health care worker who assesses and guides the patient through the phase of preventive monitoring. The issues that are addressed include: information on the course of the disorder in question and risk factors for relapses, the structure of mental health care networks and ways of optimised use of services and treatments (including psychotropic drugs).

Additionally, individual risk factors for a potential crisis (e.g. familial, work or financial problems, accommodation etc.) and protective factors in case of a crisis (e.g. familial, social resources, behaviour etc.) are assessed. These risk and protective factors constitute an individual crisis guideline (check-list) to be discussed at the regular monitoring contacts during the follow-up period to predict signs of a crisis.

Psycho-educational instruction aims to increase the patients’ self-management skills, to enhance their overall treatment compliance and intake of psychopharmacologic drugs and to activate the patients’ potential for secondary prevention of relapses.

(b) Individualised crisis card

Based on the essential parts of the individual crisis guideline (a), a crisis card is drawn up in collaboration with the patient and handed out to the patient during the last instruction session. Crisis cards contain information on the patient, professional or personal contact persons, treatment, medication, and an individual action plan in case of a crisis or relapse.

Apart from collecting information and discussing the patient’s individual condition, this procedure deepens the relationship between patients and their personal mental health care workers and enhances the basis for trusting contacts during the follow-up. Moreover, it increases the patient’s feeling of being actively involved in his/her care. Accordingly, it is left to the patient to provide his/her regular therapist with a copy of the crisis card.

(c) Preventive monitoring of individual risk factors for compulsory re-admission to hospital

After discharge from the inpatient index episode, each patient is contacted every fourth week by telephone. These contacts will cover the complete follow-up period (24 months). Patients, however, are not visited at home. If the study participant does not answer the phone, the personal mental health care worker will follow-up until he/she gets through to the study patient. At each contact, the present status of study patients is assessed using the individual risk factor checklist. In order to assess service utilisation other scales are applied (instruments, see below). Monthly contacts are designed to provide a dense individual pattern of the course of the illness and the utilisation of health care services. Preventive monitoring enables detection of early signs of a crisis or a threatening relapse and offers opportunities to discuss issues or to intervene in case of problems.

It is only in emergency situations in which a patient may constitute a danger to himself or others, (e.g., if a study participant reports suicidal thoughts, but refuses to see any mental health care professional or other persons) that the personal mental health care worker will adopt measures to protect the study participant. Patients are informed that in such a situation the confidentiality agreement will be ignored. It is not intended, however, that the personal mental health care worker who maintains contact to the patient during follow-up communicates with a patient’s regular therapists or other mental health care professionals. Only if a patient explicitly desires this, may the personal mental health care worker impart information.

The individual data on the course of illness and care will be used to analyse a possible association with the major outcomes of the study. The recording of involuntary admissions to psychiatric hospitals, forensic facilities or prison terms during the follow-up period will allow analysis of the complex interdependencies between individual illness-related features and the pathways to institutionalised care in these sectors. Additionally, service utilisation data will be transformed into cost information and used to analyse the potential cost-effectiveness of the major study intervention (compared to treatment as usual in the control group).

## Study design

The study is a prospective controlled trial. After provision of consent, the patients at each centre are assigned consecutively at random to either the intervention or the control group (Figure 1). To generate comparable groups and to prevent accidental bias as well as possible, block randomisation is used. A block size of 10 is chosen in order to ensure a balance in the numbers of subjects. Random allocation is made until the planned centre-specific sample sizes have been met.

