### Participants

The population from which the samples are recruited consists of consecutively admitted users of inpatient mental health care in the Canton of Zurich. Included are patients who

 – have been compulsorily admitted to psychiatry at least once during the past 24 months,

 – receive inpatient treatment in one of the four psychiatric hospitals participating in the study during the recruitment period (24 months),

 – are aged 18–65 years,

 – are residing in the Canton of Zurich,

 – and are willing and able to consent.

Patients who cannot be contacted by telephone (no telephone or mobile phone available) or who lack sufficient language skills are not eligible for inclusion.

Participation is not bound to a specific mental disorder. To be included in the study, however, patients must not have been diagnosed (index episode) with an organic mental disorder (ICD-10 F0), mental retardation (F7), a behavioural syndrome associated with physical factors (F5) or a developmental or behavioural disorder with onset usually occurring in childhood and adolescence (F8-F9).

The study sample is recruited from a naturalistic user sample from four study centres, all of them psychiatric hospitals mandated to provide psychiatric care to adult patients in the Canton of Zurich. Collaborating study centres are: Integrated Psychiatry Winterthur - Zürcher Unterland, Psychiatric Hospital Sanatorium Kilchberg AG, Clinic of Affective Disorders and General Psychiatry, Clinic for General and Social Psychiatry, Psychiatric University Hospital Zurich. At each study centre one designated mental health care worker is in charge of the study participants from that institution.

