#### Data analysis and statistical power

All major endpoints of the study will be compared between the intervention and the control group. Primary outcome of the study is the time in hospital accumulated over all involuntary inpatient stays during the 24 month period. This outcome criterion will be analysed in terms of both “time in hospital” and savings of health care budgets (“health care costs”).

As further endpoints of the study (secondary outcome criteria) changes in the perspective of the patients are assessed. Hypothesised benefits of the intervention are a reduction of institutionalised care and coercion. Lower levels of subjectively experienced coercion are supposed to be associated with a respective increase in quality of life, treatment satisfaction and level of empowerment.

To address the major research questions, the quantitative outcome data will be analysed for the whole trial across the four centres, using General Linear Models. T-tests for independent samples are applied primarily to test the comparability of the intervention and the control group. Analyses of covariance are performed to compare the intervention and the control group with respect to the primary outcome (time in hospital accumulated over all involuntary inpatient stays) and secondary outcomes (reduction in levels of subjectively experienced coercion; increase in quality of life, treatment satisfaction and level of empowerment). Age, gender, centre and other variables which show significant between-group differences are included in the GLM models as covariates. To examine which characteristics on the patient level (treatment history, diagnosis, social network, treatment adherence in the two-year follow-up) modify the outcome, we examine the effects of these variables on the outcomes of interest within the intervention group, applying regression analyses. The level of significance is set at 0.05, two-tailed.

The planned overall sample size across all centres is 400 patients, of which 200 each will be assigned to the intervention group or to the control group. So each centre is expected to contribute 100 patients (50 intervention group and 50 control group).

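### A single published block size of 10 makes about one allocation in six certain to anyone tracking a centre's assignments; undisclosed, varying block sizes are a cheap improvement

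*Protocol article*

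**What the plan says.** The Study design section states that after consent "the patients at each centre are assigned consecutively at random to either the intervention or the control group". It then fixes the block: "A block size of 10 is chosen in order to ensure a balance in the numbers of subjects". Allocation runs to a set total per centre: "Random allocation is made until the planned centre-specific sample sizes have been met". The section on data analysis and statistical power gives that total: "So each centre is expected to contribute 100 patients (50 intervention group and 50 control group"). Four centres make 400.

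Two other sections show who learns the allocations. Under Participants: "At each study centre one designated mental health care worker is in charge of the study participants from that institution". Under Intervention: "All measures are provided by a personal mental health care worker (psychologist"), with the first sessions held straight after randomisation and before discharge. The same section says that the regular treatment team is not told the result of randomisation. The section on informed consent says that every eligible patient at the centres is approached before a planned discharge. The article does not say who makes that approach or takes consent.

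**The concern.** In a block of known, fixed size, the remaining assignments are determined once one arm has used up its places. The knowledge comes from past allocations, so concealing the next assignment does not prevent it. Here the size is a single number printed in a public article, and one person per centre necessarily learns which patients enter the intervention arm.

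If someone with that knowledge also had a say in when a patient is approached, or how firmly, patients with a better or worse outlook could be steered towards one arm. The planned covariates (age, gender, centre and variables that differ significantly between groups) could not be relied on to repair that, because the steering may act on features that were not measured. The Study design section justifies blocking by balance and by protection against chance differences. It does not address predictability.

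**Working it through.** **Inputs from the protocol article**
- Block size B = 10, one fixed size (Study design).
- Ratio 1:1, so five per arm in each block; 100 patients per centre and 400 in all (data analysis and statistical power). This is 100/10 = 10 complete blocks per centre and 40 in the trial.
- Blocks run within centre. This is inferred from the wording that patients are assigned at each centre up to centre-specific totals; it is not stated outright.

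**The plan's own figure.** The article gives no figure for predictability. Its only related number is the sample size, which reproduces. With CV 1.25, sigma = sqrt(ln(1 + 1.25²)) = 0.970; the difference is |ln(25/33)| = 0.278; at two-sided 5% and 80% power the normal formula gives 192 per group and the noncentral t gives the stated 193. This point leaves that number untouched.

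**Allocations certain in advance.** Count the assignments in a block that come after one arm has reached five. The expected number is B/(B/2 + 1) = 10/6 = 1.67. Enumerating all C(10,5) = 252 arrangements gives the same value.
- Share of patients: 1.67/10 = 16.7%.
- Per centre: 10 × 1.67 = 16.7 of 100.
- Whole trial: 40 × 1.67 = 66.7, about 67 of 400.
- The last place in every block is always known. Two or more are known in 4/9 = 44.4% of blocks.

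**Best guess.** Always guessing the arm that lags within the block gives 5 + (2^10/252 − 1)/2 = 6.53 correct of 10, or 65.3%, against 50% by chance.

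**Other fixed sizes, same formula**

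| Block size | Certain in advance |
|---|---|
| 4 | 33.3% |
| 6 | 25.0% |
| 8 | 20.0% |
| 10 | 16.7% |
| 12 | 14.3% |

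**Hidden, randomly varying sizes.** Simulation of 1,500 lists of 100 patients. The observer sees every allocation and knows the set of sizes, but not the size of the current block. Sizes are drawn with equal probability (an assumption).

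| Sizes | Certain in advance | Best guess correct |
|---|---|---|
| 10 only | 16.7% | 65.3% |
| 8, 10, 12 | 1.3% | 64.9% |
| 6, 8, 10 | 1.7% | 66.3% |
| 4, 6, 8 | 2.4% | 67.9% |

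These figures are for freely drawn sizes. If a list is built to end exactly at 100 and the observer knows that, the last run at the centre also becomes known. Its expected length is at most 12/7 = 1.7 patients, which takes 8/10/12 to roughly 1.3% + 1.7% = 3%.

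**The case against.** A reader might infer that each centre's worker does know one allocation in six before enrolment, and that the comparison is therefore biased. The documents do not support that, for these reasons.

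- **No recruiter is named.** The worker's described tasks are education, the crisis card, monitoring and charge of participants. Selection bias needs control over entry as well as knowledge.
- **Approach and allocation are described as exhaustive and consecutive.** All eligible patients are to be asked, which leaves little room over whom to approach. It does not settle when they are asked or how strongly.
- **The treating team is masked.** It would ordinarily decide discharge, and it could not predict from its own knowledge.
- **The caseload shows intervention patients only.** Certainty also needs the number of controls and the start of each block. Being in charge of a centre's participants makes this plausible, but it is not stated.
- **Recruitment may already be over.** The abstract says that the study is being conducted, and 24 months of follow-up come after 24 months of recruitment. Publishing the size matters only if patients remain to be randomised.
- **Ten is already less predictable than fixed blocks of 4, 6 or 8.**

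It is also tempting to quote a bias in days. Multiplying 16.7% by an assumed 5 to 10 day difference gives 0.8 to 1.7 days. The difference appears nowhere in the article, and the product requires every forced place at all four centres to be recognised and used in one direction. It is not an estimate.

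All of this stands, and it makes the point conditional. It does not remove the weakness: the size is fixed and printed, and one person per centre cannot be masked. The selection bias that the article itself expects from the consent procedure is a different matter. It concerns who enters the trial, not which arm they enter.

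Who generates and holds the list is detail that an article leaves to the full protocol, and its absence is no finding.

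**Conclusion.** The point holds as a cheap improvement, not as a demonstrated bias. A fixed block of 10 within centre makes 16.7% of allocations, about 67 of 400, certain in advance to a person who knows the size, knows where blocks start and follows all of that centre's allocations. That share is exact under the inferred assumption that blocks run within centre. Whether anyone held that knowledge and could also act on enrolment is not stated, so the size of any effect on the primary outcome cannot be derived from the documents. Varying the block size would remove most of the certainty, but almost none of the advantage from guessing.

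**What to change.** For all patients still to be randomised, replace the block-size sentence in the Study design section with: *permuted blocks of randomly varying size, stratified by centre, with sizes not disclosed to centre staff*. Sizes of 8, 10 and 12 are one workable set, arranged to sum to each centre's target and without telling centre staff that they do.

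The cost is a new list per centre and one changed sentence. A centre that stops in the middle of a block of 12 could be out of balance by up to 6. With fixed tens, a centre that completes its 100 has no imbalance, and one that stops mid-block can be out by up to 5.

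If recruitment has closed, no change to the lists is possible. The sponsor should then report who enrolled patients at each centre, and whether those people knew the block size and the earlier allocations.

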**Figure 1 F1:**
[figure not shown]
Flowchart.

The intervention is applied during a 24-month period. In both, the intervention and the control modality patients receive treatment as usual, i.e. regular out- or inpatient mental health care as offered in the respective study region.

The study encompasses a baseline assessment during the inpatient episode (t0) and a one-, respectively two-year follow-up (t1; t2). This applies to both the intervention and the control group. To enhance the compliance to contacts and assessments, each study participant (in the intervention and in the control group) receives an expense allowance of 60 CHF that is paid in instalments of 10 CHF at t0 and 25 CHF each at t1 and t2.

### Participants

The population from which the samples are recruited consists of consecutively admitted users of inpatient mental health care in the Canton of Zurich. Included are patients who

 – have been compulsorily admitted to psychiatry at least once during the past 24 months,

 – receive inpatient treatment in one of the four psychiatric hospitals participating in the study during the recruitment period (24 months),

 – are aged 18–65 years,

 – are residing in the Canton of Zurich,

 – and are willing and able to consent.

Patients who cannot be contacted by telephone (no telephone or mobile phone available) or who lack sufficient language skills are not eligible for inclusion.

Participation is not bound to a specific mental disorder. To be included in the study, however, patients must not have been diagnosed (index episode) with an organic mental disorder (ICD-10 F0), mental retardation (F7), a behavioural syndrome associated with physical factors (F5) or a developmental or behavioural disorder with onset usually occurring in childhood and adolescence (F8-F9).

The study sample is recruited from a naturalistic user sample from four study centres, all of them psychiatric hospitals mandated to provide psychiatric care to adult patients in the Canton of Zurich. Collaborating study centres are: Integrated Psychiatry Winterthur - Zürcher Unterland, Psychiatric Hospital Sanatorium Kilchberg AG, Clinic of Affective Disorders and General Psychiatry, Clinic for General and Social Psychiatry, Psychiatric University Hospital Zurich. At each study centre one designated mental health care worker is in charge of the study participants from that institution.

### Informed consent, data security and ethical approval

During the recruitment period all patients in the study centres fulfilling the inclusion criteria are informed (verbally and in written form) about the study and asked for their written consent prior to a planned discharge.

Personal data are treated according to the privacy regulations of the Psychiatric University Hospital Zurich, based on Art. 51 Personalgesetz (Human Resources Law). The results of the participant questionnaires and all interview data are accessible only to members of the study staff, but not to doctors or mental health care workers. The complete study protocol was endorsed by the Ethical Review Board for Clinical Studies of Canton Zurich, for Clinical Studies of Canton Zurich.

All study-related documents and data are stored on a protected central server of the ZInEP research group. Only members of the study staff have access to the respective files.

### Measurements

At baseline (t0) and again after 12 (follow-up t1) and 24 months respectively (follow-up t2), data on patient characteristics and health care use are gathered by means of face-to-face interviews and questionnaires. Interviews with study participants (intervention and control patients) are conducted by the members of the study staff.

Baseline assessment is scheduled upon discharge from the index episode at one of the study centres. Additional data concerning individual risk factors and service utilisation are collected during the monthly telephone contacts between the patient and his/her personal mental health care worker (intervention group).

As the overall number of questions at baseline assessment is high, a limited number of scales will be applied at the t1- and t2-follow-ups to limit the burden on patients and to comply with restricted time resources available for the interview session. Table 1 provides an overview of the measurements and the instruments used at the different time points.

**Table 1 T1:** Outcome measures

**Variables**	**Instrument**	**Time of assessment**
Sociodemographic data	Patient file; CSSRI-EU	t0, t1, t2
Utilisation of mental health care or other relevant services (Previous health care use; number and length of voluntary and involuntary psychiatric inpatient episodes; frequency and length of stays in forensic facilities, frequency of use of outpatient psychiatric care and of other services during follow-up)	CSSRI-EU	t0, t1, t2 continuously in the intervention group; every 3 months in the control group
Psychopathology	CGI; GAF; OQ- 45; BPRS	t0, t1, t2
Risk of self-harm or threat to others	Patient file; HCR-20; PCL-SV; BPRS	t0, t1, t2
Informal coercion/perceived coercion	MacArthur AES	t0
Empowerment	Empowerment-Scale	t0, t1, t2
Treatment satisfaction	CSQ-8	t0, t1, t2
Quality of life	WHO-QoL-Bref	t0
Social support	BSSS	t0
Internalised Stigma	Internalised Stigma of Mental Illness Inventory	t0, t1, t2
Self-esteem; Cognitive appraisal of stigma as a stressor; Emotional reactions to compulsory admission	Rosenberg Self-Esteem Scale; Stigma-Stress Scale; 4 items	t0

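### As written, baseline (t0) falls after randomisation and after the intervention arm's inpatient sessions, so t0 scales may carry an early treatment effect into covariate selection and change scores

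*Protocol article*

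**What the plan says.** All references are to the protocol article.

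- **Study design, allocation:** "After provision of consent, the patients at each centre are assigned consecutively at random" to one of the two arms. No assessment is named between consent and allocation.
- **Intervention, part (a):** "Immediately after recruitment and randomisation, each study patient in the intervention group attends the initial" sessions, one to three in number. On their timing: "The sessions are scheduled prior to discharge from the index episode".
- **Intervention, part (b):** the crisis card is "handed out to the patient during the last instruction session". The article describes no instruction sessions after discharge, only telephone monitoring.
- **Measurements:** "Baseline assessment is scheduled upon discharge from the index episode at one of the study centres".
- **Study design, after the flowchart:** t0 is placed within the inpatient stay, with no statement of whether it comes before or after allocation. The flowchart itself is not shown in the text available.
- **Table 1:** empowerment, treatment satisfaction and psychopathology are measured at t0, t1 and t2. Quality of life is listed at t0 only.
- **Data analysis and statistical power:** t-tests check whether the arms are comparable. Age, gender, centre and any other variable that differs significantly between arms then enter the linear models. Secondary outcomes are worded as reductions or increases.

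**The concern.** A baseline is useful as a covariate or reference because allocation cannot have changed it. A t0 taken at discharge does not have that property here. The sessions and the card aim at self-management, adherence, a trusting relationship with the personal worker and a sense of involvement in one's own care. The empowerment and satisfaction scales at t0 measure these things or close neighbours of them.

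Two consequences follow. First, the comparability t-tests would partly test an early treatment effect, and the covariate rule would then favour the variables the intervention has moved. Adjusting for such a variable removes part of the effect and gives up the protection of randomisation for that part. Second, any analysis of change from t0 would measure only what happened after the sessions, so the early contribution of the psycho-education and the crisis card would be lost. At stake is mainly the estimate for the patient-reported secondary outcomes. A true baseline cannot be recovered afterwards.

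**Working it through.** **1. Order of events.** Reading the sections together, the intervention arm runs: consent, randomisation, one to three sessions with the crisis card at the last, discharge with t0. The control arm runs: consent, randomisation, discharge with t0. The looser statement in Study design fits this order but does not require it. No section shown places t0 before allocation or before the first session.

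**2. The plan's own sample size.** Inputs from Data analysis and statistical power: means of 33 and 25 days, CV 1.25, log-normal, two-sided 5%, power 80%.
- SD on the log scale = √ln(1 + 1.25²) = 0.970
- Difference on the log scale = ln(33/25) = 0.2776
- n per group = 2 × (1.960 + 0.842)² × 0.970² / 0.2776² ≈ 192 with the normal approximation, and 193 with the noncentral t

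The stated 193 reproduces, and the timing of t0 does not affect it.

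**3. Loss when a shifted t0 scale is used.** Let e be the early shift at t0 in SD units and ρ the within-arm correlation of t0 with follow-up. The documents give neither, so both are assumed: e = 0.1 to 0.3, ρ = 0.3 to 0.7. With equal SDs at both times:
- ANCOVA estimate = true effect − ρ × e
- Change-score estimate = true effect − e

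The ANCOVA loss runs from 0.3 × 0.1 = 0.03 SD to 0.7 × 0.3 = 0.21 SD.

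**4. Chance of selection.** With 200 per arm, the probability that a shifted scale differs significantly is about Φ(e × √(200/2) − 1.96) = Φ(10e − 1.96).

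For an assumed true follow-up effect of 0.30 SD:

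| e | Chance of selection | ANCOVA estimate, ρ = 0.7 to 0.3 | Change-score estimate |
|---|---|---|---|
| 0 (true baseline) | 5% | 0.30 | 0.30 |
| 0.1 | 17% | 0.23 to 0.27 | 0.20 |
| 0.2 | 52% | 0.16 to 0.24 | 0.10 |
| 0.3 | 85% | 0.09 to 0.21 | 0.00 |

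**5. The rule as a whole.** A simulation of 4,000 trials per setting, with ρ = 0.5 and a true effect of 0.30 SD, compared always adjusting with adjusting only when the t0 difference was significant. At e = 0.2 the mean estimates were 0.20 and 0.23. At e = 0.3 they were 0.15 and 0.16. At e = 0 both were 0.30.

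**6. Primary outcome.** Accumulated involuntary days have no t0 value to subtract, and the sessions cannot change age, gender or centre. If a shifted scale did enter the model and its correlation with log days were 0.3 in size, a true reduction from 33 to 25 days would be estimated as 33 to 25.7 (e = 0.1) or 33 to 27.3 (e = 0.3). That correlation is also an assumption.

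**The case against.** The strongest counter-argument is that the order is inferred. The flowchart is not shown and could place t0 earlier. Consent is itself sought ahead of a planned discharge, so consent, t0, allocation and sessions may all fall in a short window that the Measurements section describes loosely. This limits the certainty but does not remove the point: the sentence on discharge is explicit, and if the flowchart differs, the two need reconciling.

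Other parts of the objection stand and limit the claim:

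- A reader might infer that t0 values are known to be affected. The documents show only that they may be. The size and direction are unknown, and an adverse early effect would bias the other way.
- A reader might infer that every outcome is adjusted for its own t0 value. The article does not say so, nor does it say that change scores are analysed. Adjustment comes through the significance rule; change is only suggested by the wording of the outcomes.
- A reader might extend the problem to all secondary outcomes. Table 1 lists quality of life at t0 only. The t0 coercion survey asks about the admission, which precedes allocation, and its follow-up version is modified for outpatients. The mechanism fits empowerment and treatment satisfaction best, with psychopathology mainly as a candidate covariate.
- A reader might infer that t0 interviewers know the allocation. The article says only that study staff conduct the interviews.
- A reader might infer that losses between randomisation and t0 would go unnoticed. Randomised patients can be counted whether or not t0 is done, and patient-file data exist for them.

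**Conclusion.** The point holds as a fault in the stated timing combined with the covariate rule. It is not a demonstrated bias. Followed literally, the plan measures t0 after randomisation and, in the intervention arm only, after the inpatient sessions and crisis card. It then selects covariates in a way that favours whatever those sessions changed.

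Under the assumed ranges (e = 0.1 to 0.3 SD, ρ = 0.3 to 0.7), the loss is 0.03 to 0.21 SD when a shifted scale is entered, and 0.1 to 0.3 SD for a change score. Selection occurs in about 17% to 85% of trials, against 5% for a true baseline. A beneficial early effect pulls the estimate towards zero.

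The stronger reading, that the primary comparison is biased, is not supported. That comparison is exposed only if a shifted t0 scale enters its model, which the rule permits but does not require.

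**What to change.** 1. State that t0 is completed after consent and before randomisation in both arms, or at the least before the first instruction session. Bring Study design, Measurements and the flowchart into line with this.
2. Replace covariate selection by significance test with a prespecified list that allocation cannot affect: age, gender, centre and chart-based prior service use.
3. For patients already enrolled whose t0 followed a session, treat the t0 scales as post-randomisation data and use them neither as covariates nor as change references. Handle control patients recruited over the same period in the same way, so that the arms remain comparable.

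**Cost:** existing steps are re-ordered within the inpatient stay and no new procedure is needed. The downside is that t0 is done somewhat earlier, so scales that describe the stay cover less of it. The sample size of 193 per group, with 200 planned, is unchanged.
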